### Dietary and psychological status assessments

2.4.

For all three study groups, information obtained from clinical records is collected. Anthropometric data (e.g., weight, height, and head circumference), sociodemographic, dietary, other relevant information related to lifestyle (e.g., smoking habits, sleep hours, and physical activity), and psychosocial status are provided through questionnaires by participating mothers as summarized in Table 1. As shown in Figure 1, 24 h dietary recalls are recorded at all timepoints except at birth, food frequency questionnaire (FFQ) at month 1, maternal psychosocial status at CEN/RBW and month six (corrected age for PI groups), and infant neurodevelopment at months six and twenty-four. The questionnaires are administered online, on paper, or through direct interviews with the mothers.

**Table 1 T1:** Recorded parameters from lactating mothers and infants.

Assessment	Parameter
Nutrition	FFQ
	24-hour dietary recall
Clinical data	Maternal conditions
	Pregnancy complications
	Delivery type
	Medical information
	Maternal medication
	IIFAS
	Infant's gestational age
	Infant sex
	Infant diagnosis
	Perinatal complications
Sociodemographic data	Origin
	Education
	Household income
	Employment status
Lifestyle	Smoking habits
	Physical activity
	Sleeping habits
Anthropometric data	Maternal weight
	Infant height
	Infant head circumference
Psychosocial status	MSPSS
	FACES
	PSS-10
	STAI
	EPDS
	BDI
	TEQ
	PBQ
	PSI
Infant neurodevelopment	ASQ-3
	IBQ
	Merril-Palmer revised scales

FFQ, Food Frequency Questionnaire; IIFAS, Iowa Infant Feeding Attitude Scale; BMI, Body Mass Index; MSPSS, Multidimensional Scale of Perceived Social Support; FACES, Family Adaptability and Cohesion Evaluation Scale; PSS-10, Perceived Stress Scale-10; STAI, State-Trait Anxiety Inventory; EPDS, Edinburgh Postnatal Depression Scale; BDI, Beck Depression Inventory; TEQ, Traumatic Experience Questionnaire; PBQ, Postpartum Bonding Questionnaire; PSI, Parenting Stress Index; ASQ-3, Ages & Stages Questionnaires; IBQ, Infant Rothbart's Temperament Questionnaire.

Regarding the 24 h recall, trained researchers ask for all foods and beverages participants consumed during the previous day, using the multiple-pass method (43). Recall data are analyzed in terms of nutrients using the dietary analysis software Nutritionist Pro™ (2007, Axxya Systems, Texas, USA). Additionally, dietary intake is grouped into food groups, (i.e., fruits, vegetables, bread/starch, meat/high fat, meat/medium fat, meat/low fat, meat/very low fat, milk/non-fat, milk/low fat, milk/full fat, eggs, fish, soy, dairy products, soft drinks, and other carbohydrate-rich foods).

The FFQ is administered by trained personnel, and it comprises 142 questions on the consumption of foods that are commonly eaten by the Spanish population throughout a year, including dairy products, cereals, fruits, vegetables, meat, fish, legumes, added fats, alcoholic beverages, stimulants, and sweets. Using a 9-grade scale (“never or less than 1 time/month”, “1–3 times/month”, “1 time/week”, “3–4 times/week”, “5–6 times/week”, “1 time/day”, “2–3 times/day”, “4–5 times/day”, “≥6 times/day”) participants are required to indicate the absolute frequency of consuming a certain amount of food, expressed in grams, milliliters or in other common measures, such as slice, tablespoon, or cup, depending on the food. The previous month is set as the timeframe. The FFQ is an easy-to-use questionnaire and is not expected to increase the burden of lactating mothers.

Based on the FFQ-responses, adherence to the Mediterranean diet is evaluated by using the MedDietScore, a composite score calculated for each participant (44). For food groups presumed to be part of the Mediterranean pattern (i.e., those with a recommended intake of 4 servings per week or more, such as non-refined cereals, fruits, vegetables, legumes, olive oil, fish, and potatoes) higher scores are assigned when the consumption is according to the rationale of the Mediterranean pattern, while lower scores are assigned when participants report no, rare, or moderate consumption. For the consumption of foods presumed to be eaten less frequently within the Mediterranean diet (i.e., consumption of meat and meat products, poultry, and full fat dairy products), scores are assigned on a reverse scale. As this study is focused on lactating mothers, the original score was modified by removing the alcohol consumption component. Thus, the range of this modified MedDietScore is between 0 and 50, with higher values of the score indicating greater adherence to the Mediterranean diet.

Maternal psychosocial status is measured at recruitment and at six months, including social support [Multidimensional Scale of Perceived Social Support, MSPSS (45)], family functioning [Family Adaptability and Cohesion Evaluation Scale, FACES (46)], perceived stress [Perceived Stress Scale -10, PSS-10 (47)], anxiety [State-Trait Anxiety Inventory, STAI (48)], depression [Edinburgh Postnatal Depression Scale, EPDS (49), Beck Depression Inventory (BDI) (50)] symptoms, and traumatic life events [Traumatic Experience Questionnaire, TEQ (51, 52)]. Mother-infant postpartum bonding [Postpartum Bonding Questionnaire, PBQ (53)] and parental stress [Parenting Stress Index, PSI (54)] are also examined.

As for the infants, at six and twenty-four months (corrected age for PIs) assessment of neurodevelopment is conducted during a hospital visit by a trained psychologist and psychiatrist from the team. Parents complete the Ages & Stages Questionnaires, Third Edition (ASQ-3) (55) for psychomotor development evaluation and the Infant Rothbart's Temperament Questionnaire (IBQ) (56) for infant temperament. The ASQ is a well standardized instrument used in clinical and research practice to examine children's psychomotor development gathering items in five domains: communication, gross motor, fine motor, problem solving, and personal-social. Clinical observation and Merrill-Palmer revised scales (57) for development are applied during the session.

Mother's concerns and attitudes to breastfeeding are also registered through the Iowa Infant Feeding Attitude Scale (IIFAS) (58) at CEN/RBW and six months.

Milk donors are asked to provide sociodemographic, medical, dietary, and other lifestyle data. PSS-10 is evaluated when entering the study in order to correlate with hormones and other compounds present in the milk. In particular, each time a batch of milk is prepared, a FFQ is administered (representing the period of time that the batch of milk covered) and the donors are asked to provide medical, anthropometric, and lifestyle data.

### Analysis of biological samples employing laboratory methods

2.5.

A range of state-of-the-art as well as novel laboratory methods are employed for the analysis of the collected biological samples, as summarized in Table 2.

**Table 2 T2:** Analysis of biological samples employed.

Analysis	Parameters	Technique	Matrix
Genome	Whole genome sequencing	Illumina NovaSeq	Buccal swab
Microbiota	Bb species	ATGC	Faeces
			HM
Microbiota activity	SCFAs BCAAs	GC-MS	Faeces
			Urine
			HM
	Bas	LC-MS/MS	Urine
Nutrition	Flavonoids	LC-MS/MS	Urine
	Isoflavones		
	Arylglycines		
	Amino acids		
Metabolome	Metabolomic fingerprinting	LC-HRMS	Urine
Macronutrients	Fat	Miris HM analyzer	HM
	Carbohydrates		
	Crude & true protein		
	Total solids		
	Energy		
Fatty acids	34 fatty acids (C6-C24)	GC-MS	HM
	SAT	HM fatty acid sensor	
	MONOs		
	PUFAs		
	UNSAT		
	SCFAs		
	MCFAs		
	LCFAs		
Vitamins	Vitamin B, D and K groups	LC-MS/MS	HM Umbilical cord blood
	Retinol forms	LC-UV	
	Carotenoids and vitamin E groups	LC-UV/Fluorescence	
HMOs	HMO screening	LC-HRMS	HM
Steroids	19 steroid hormones	LC-MS/MS	HM
			Urine
Proteins	Total protein	HM protein sensor	HM
	Alpha-lactalbumin		
	Lactoferrin		
	Casein		
pH	pH	Urine pH sensor	Urine
Phosphate and creatinine	Phosphate and creatinine	Phosphate and creatinine sensor	Urine

ATGC, Advanced Testing for Genetic Composition; Bb, Bifidobacterium; GC, Gas Chromatography; (HR)MS, (High Resolution) Mass Spectrometry; SCFAs, Short Chain Fatty Acids; BCAAs, Branched Chain Amino Acids; Bas, Bile Acids; SAT, saturated fatty acids; MONOs, monounsaturated fatty acids; PUFAs, polyunsaturated fatty acids; UNSAT, unsaturated fatty acids; MCFAs, medium-chain fatty acids; LCFAs, long-chain fatty acids; LC, Liquid Chromatography; UV, Ultraviolet; HMOs, Human Milk Oligosaccharides.

#### Genome sequencing

2.5.1.

For genome sequencing analysis, DNA extraction from buccal swab samples takes place according to the protocol developed by the sequencing provider facility. Polymerase chain reaction (PCR) quality control (QC) is performed before samples are shipped to the sequencing service provider, and again upon receival by the sequencing facility. QC and library preparation follow the Illumina NovaSeq protocol (Paired End, 150 bp). Three polygenic risk scores (PRS) models are developed for body mass index (BMI), diabetes type 2, and lactose intolerance, calculated by Plink software (59), and the resulting genotype files, one per sample, are then used as separate input to the PRS models.

This score can then be compared to the scores obtained from the UK Biobank set (60), to estimate the relative risk for this individual compared to the rest of the UK Biobank individuals (∼370.000 individuals), which are split in 10 quantiles according to their genetic risk.

#### Microbiota analysis

2.5.2.

Advanced Testing for Genetic Composition (ATGC) is used for microbiota analysis of faeces and HM samples (61). It is a targeted measurement technique that provides greater precision, specificity, and versatility than rtPCR, while being just as cost-effective and fast. It has been developed to translate discovery data from untargeted analysis (e.g., 16S or shotgun meta-genomics) into tests for routine use.

The Bifidobacterium (Bb) assay used is specifically designed to analyze the main species and subspecies varieties in HM and newborn gut microbiomes. For sample processing, the HM lipid layer is solubilized using a detergent, while for faeces, a lysis step using a lysis buffer with bead beating for 20 s is required. Then, an in-house DNA extraction procedure and a PCR are carried out. Cycling temperature capillary electrophoresis (CTCE) is made for each primer on an independent capillary. It is performed on a MegaBace 1,000 instrument (General Electrics, Boston MA, USA) as described earlier (62).

#### Microbiota activity biomarkers analysis

2.5.3.

The microbiota activity is evaluated with the following methods:
(i)Short chain fatty acids (SCFAs) and branched chain amino acids (BCAAs) in faeces, urine and HM samplesSCFAs (i.e., acetic, propionic, isobutyric, butyric, 2-methylbutyric, isovaleric, valeric, caproic and heptanoic acids) and BCAAs (i.e., valine, leucine and isoleucine) are determined by targeted gas chromatography coupled to mass spectrometry (GC-MS), as described elsewhere (63, 64), using an Agilent 7890B GC system coupled to an Agilent 5977A quadrupole MS detector (Agilent Technologies, Santa Clara, CA, USA).
(ii)Bile acids (BAs) in urine samplesIn total, 34 BAs (6 primary, 7 primary conjugated, 5 secondary, 10 secondary conjugated and 6 sulphated) are determined in urine samples by liquid chromatography coupled to tandem MS (LC-MS/MS), as described elsewhere (65) with minor modifications, using an ACQUITY LC chromatograph (Waters Ltd, Elstree, UK) coupled to a Xevo TQ-S MS detector (Waters, Manchester, UK).

#### Nutrition biomarkers analysis

2.5.4.

Quantification and semi-quantification of 20 and 205 urinary nutrition biomarkers (e.g., flavonoids, isoflavones, and arylglycines), respectively, related to nine food groups such as fruits, vegetables, meat, fish, dairy products, milk, seeds, coffee, and soft drinks is carried out (66, 67). Additionally, seven microbiota activity biomarkers are determined using this method (i.e., phenylpropionylglycine, L-kynurenine, L-tyrosine, hippuric acid, 3-indolepropionic acid, ferulic acid sulphate and 3-indoleacetic acid). LC-MS/MS analysis is conducted using a Sciex QTRAP 6500 + system (Sciex, Framingham, Massachusetts, USA).

#### Untargeted metabolomic fingerprinting

2.5.5.

Untargeted metabolomic analysis is carried out in urine samples by LC-MS/MS, employing an Agilent 1,290 Infinity HPLC system coupled to an Agilent 6,550 Spectrometer iFunnel quadrupole time-of-flight (QTOF) MS detector (Agilent Technologies, Santa Clara, CA, USA), as previously described (68).

#### Macronutrients analysis

2.5.6.

Direct measurement of HM macronutrients including fat, carbohydrates, crude and true proteins, total solids, and energy are determined using a Miris HM analyzer (Miris AB, Uppsala, Sweden). Determinations, QC, and instrument calibration are performed following the SOP provided by the manufacturer (69).

#### Fatty acid profile analysis

2.5.7.

The targeted analysis of 36 fatty acids in HM samples is carried out by GC-MS as described elsewhere (70, 71), using an Agilent 7890B GC system coupled to an Agilent 5977A quadrupole MS detector (Agilent Technologies, Santa Clara, CA, USA).

#### Vitamin analysis

2.5.8.

Quantification of water-soluble (group of vitamin B: thiamine, thiamine monophosphate, riboflavin, flavin adenine dinucleotide, nicotinamide, pyridoxal and pyridoxal phosphate) and lipid-soluble vitamins (group of vitamin A: retinol forms, β-carotene, β -cryptoxanthin, lutein, lycopene and zeaxanthin; group of vitamin E: α-tocopherol and γ-tocopherol; group of vitamin K: phylloquinone and menaquinone-4; group of vitamin D: cholecalciferol and calcifediol) in HM and umbilical cord blood samples is carried out.

The analysis of B, D and K vitamins are determined as described somewhere (72–76), using an Acquity LC chromatographic system (Waters AG, Switzerland) hyphenated to a Xevo TQ-S mass spectrometer (Waters AG, Switzerland).

The retinol forms are analyzed as previously described (75), using a LC using a quaternary Flexar chromatographic system (Perkin Elmer, Switzerland) with UV detection (325 nm).

Carotenoids and vitamin E analysis is carried out as previously described (77), using a binary Acquity LC chromatographic system (Waters AG, Switzerland) with multiple UV detection (295 nm, 450 nm and 472 nm) and fluorescence detection (exc. 296 nm/em. 330 nm).

#### Oligosaccharides analysis

2.5.9.

HMOs analysis is carried out by LC-MS in accordance with a previously described protocol (78, 79) with some modifications, employing a Vanquish LC Binary Pump coupled to an Orbitrap QExactive Plus MS detector (ThermoFisher, Waltham, MA, USA).

#### Steroid analysis

2.5.10.

Steroid analysis of HM and urine samples is carried out on an Acquity UPLC system (Waters Ltd, Elstree, UK) coupled to a Waters Xevo TQ-S MS detector (Waters, Manchester, UK) as previously described (80, 81). A panel of 19 steroids is targeted (i.e., cortisol, 5β-tetrahydrocortisol, 6β-hydrocortisol, 20α-dihydrocortisol, 20β-dihydrocortisol, corticosterone, aldosterone, estrone, androstenedione, dehydroepiandrosterone, progesterone, 17-hydorxy-progesterone, pregnenolone, cortisone, 20α-dihydrocortisone, 20β-dihydrocortisone, 6α-hydroxycortisone, testosterone, and 5α-dihydrotestosterone).

### Sensor prototypes

2.6.

Due to the special requirements of the study, three sensor prototypes enabling the determination of complementary parameters in HM and urine samples are being developed and benchmarked within the NUTRISHIELD study.

#### HM protein sensor

2.6.1.

Direct quantification of the most abundant proteins (i.e., casein, *α*-lactalbumin, and lactoferrin) in HM milk is performed using quantum cascade laser-based mid-infrared (QCL-IR) spectroscopy (82, 83). Laser-based IR spectroscopy enables more robust and sensitive analysis in the spectral region of IR signatures of proteins compared to conventional Fourier-transform infrared (FTIR) spectrometers (82). Reference protein analysis is carried out using specific Kjeldahl and HPLC analysis. Within the study, a dedicated QCL-based protein analyzer for HM is developed and benchmarked.

#### HM fatty acids sensor

2.6.2.

HM fatty acid profiling is performed based on mid-IR spectroscopy of an extracted lipid HM fraction. For analysis, 15 µl of the pure fat are transferred onto a diamond single bounce attenuated total reflection (ATR) accessory (Platinum ATR, Bruker, Ettlingen) connected to a Tensor 37 (Bruker, Ettlingen) FTIR spectrometer (84, 85).

#### Urine pH sensor

2.6.3.

A custom-made portable system based on potentiometric measurements and screen-printed electrode technology is developed to measure pH in urine. The system works with small sample volumes (i.e., 50 μl) and no dilution is needed. An additive is spiked into samples prior to measurement in order to preserve and regenerate the sensor's surface, which extends sensor lifetime to multiple uses with no carry-over between urine samples.

#### Urine phosphate and creatinine sensor

2.6.4.

Quantification of phosphate and creatinine in urine samples is performed using a method based on FTIR transmission spectroscopy. Within the study, a dedicated QCL-based urine analyzer is developed. Reference values for phosphate are obtained by a colorimetric determination after reaction of inorganic phosphorus with ammonium molybdate, while creatinine reference values are obteined following the manufacturer's instructions of the modified Jaffe's method implemented in the DetectX® urinary creatinine detection kit from Arbor Assays (Ann Arbor, MI, USA).

### Statistics and data integration

2.7.

The Student's *t*-test, Wilcoxon ranksum test or *Χ*^2^ test with *α* = 0.05 will be used for between-group comparisons and fold changes (FC) will be calculated as the ratio of means or medians between groups in accordance to the underlying distribution of the data. Pearson's linear or Spearman rank correlation coefficients will be determined between continuous variables. If necessary, partial correlation coefficients adjusting for known confounding factors will be computed. The false discovery rate (FDR) from the *p*-values of multiple-hypothesis testing will be estimated using the Benjamini and Hochberg procedure (86) and adjusted *p*-values <0.05 will be considered statistically significant.

One of NUTRISHIELD secondary objectives is the development of a personalized nutrition system based on measured biomarkers. The system is to be made available to medical personnel, as well as mothers, to improve infant-mother dyads' health and wellbeing. The results and the associations revealed from the study will be used to train a personalized nutritional algorithm with data obtained from clinical settings. This will be used to build and validate the NUTRISHIELD platform, describing how a theoretical framework designed and fed by the patients' data translates to clinical practice. Toward that goal, a comprehensive data integration system has been developed as the Clinical Trial App (CTA). The CTA is a system intended for personalized medicine/nutrition, implementing the following main features: (i) data acquisition from questionnaires, (ii) data acquisition from laboratory biomarker analysis, (iii) processing data to train machine learning algorithms, and (iv) deploying trained algorithms to produce reports for final users.

Figure 3 shows the data flow and functionalities of the CTA. Questionnaires data are collected by medical staff directly using the phone app. Alternatively, questionnaires that have been collected on paper or on spreadsheets, can be uploaded as well. All samples can be identified with a unique QR code and, at the moment of collection, the phone app can be used to scan the QR code and input sample data. This way the samples can travel between labs with the QR code as only identification. The QR code can be scanned again to associate the results with the original sample when uploading it through the web portal. The collected data is stored on a database and used to feed the personalized recommendation algorithm. This algorithm produces a report and feeds it back to the phone app.

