### Study design

2.1.

The NUTRISHIELD study is a parallel group, non-randomized, observational study performed at the Division of Neonatology of the University & Polytechnic Hospital La Fe (HULAFE), including TI and PI and their mothers, covering the period from birth to 24 months of infant's age. In addition, mothers providing DHM to study participants are also included.

The study protocol has been approved by the Scientific and Ethics Committee for Biomedical Research (CEIm) of the HULAFE (#2019-289-1). All methods have been performed in accordance with the relevant guidelines and regulations and written permission has been obtained from mothers or legal representatives by signing an informed consent form.

Confidentiality of subjects is maintained during the study. All participants have been assigned a code and data allowing personal identification will not be shared at any time. Participants may withdraw consent for participating in the study at any time.

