### Study population and recruitment

2.2.

Participants were recruited at the end of pregnancy (when admitted to the obstetric ward) or within one week after birth in case of hospitalized infants at HULAFE. Recruitment started in October 2020 and was completed in July 2022. Three mother-infant groups were enrolled, i.e., PI fed with OMM (PI-OMM), PI fed with pasteurized DHM (PI-DHM), and TI receiving OMM (TI-OMM), and their mothers.

The inclusion criteria were (i) acceptance of the mother to participate and sign an informed consent form, (ii) a gestational age <32 weeks for the group of PI and >37 weeks for the group of TI, and (iii) exclusive consumption (i.e., >80% of total intake) of either OMM or DHM at time point CEN (complete enteral nutrition, 150 mL/Kg/day) for PI or RBW (recovery of birth weight) for TI. Although the type of feeding of PIs included in either group (PI-OMM or PI-DHM) may have changed at later time points, they remained in the same study group, so the effect of feeding of each type of milk at CEN and its long-term effects can be studied. Likewise, the use of infant formula and the initiation of weaning at later time points was recorded without affecting follow-up assessments. The exclusion criteria were (i) non-compliance with any of the inclusion criteria, (ii) the requirement of a special diet for the mother (e.g., celiac disease, diabetes) or maternal consumption of probiotics, (iii) the need of intestinal surgery, severe congenital malformations, or chromosomopathies of the infant, (iv) mother's residence outside the Valencian Community and (v) severe language barriers hampering the collection of necessary data from mothers not speaking Spanish and/or English.

Sample size estimation was performed for the primary outcome (i.e., % weight gain/month from birth until hospital discharge of PI fed with DHM and OMM) and was based on result of a previous study (42). Considering the median % weight gain/month (interquartile range, IQR) of 52% (IQR: 30) in the PI-DHM group and 63% (IQR: 21) in the PI-OMM, 18 infants per group were needed to achieve a power of 90% with an alpha error of 5% between the % weight gain/month of PI exclusively receiving either OMM or DHM at CEN.

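### The only between-group tests named are unadjusted, so an imbalance in gestational age or birth size between PI-OMM and PI-DHM would be mixed with any milk effect

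*Protocol article*

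**What the plan says.** Section 2.1 calls the study a "parallel group, non-randomized, observational study". Section 2.2 forms the preterm groups by "exclusive consumption (i.e., >80% of total intake) of either OMM or DHM at time point CEN". The only restriction on maturity is "a gestational age <32 weeks for the group of PI". No matching or stratification is described. The same section gives the primary outcome as the percentage "weight gain/month from birth until hospital discharge of PI fed with DHM and OMM". It sizes the study as a plain two-group comparison, with medians of "52% (IQR: 30) in the PI-DHM group and 63% (IQR: 21) in the PI-OMM". Infants stay in the group assigned at complete enteral nutrition so that the effect of each milk can be studied.

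Section 2.7 states that Student's t-test, the Wilcoxon rank-sum test or the chi-square test "will be used for between-group comparisons and fold changes (FC) will be calculated as the ratio of means or medians between groups". Adjustment appears two sentences later, after the sentence on Pearson and Spearman coefficients: "If necessary, partial correlation coefficients adjusting for known confounding factors will be computed". The confounders are not named. Table 1 lists infant gestational age, sex, diagnosis and perinatal complications, and delivery type, among the recorded items. The limitations discussed in section 3 do not mention confounding.

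**The concern.** None of the three named tests takes a covariate. In a randomised trial that would cost only some precision. Here, group membership follows from whether the mother could supply enough milk (the Introduction gives this as the reason for using donor milk), and that may go with prematurity, maternal illness or the circumstances of delivery.

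The endpoint is exposed to the same factors by its construction. Birth weight is the base of the percentage, and time to discharge sets the window. At one and the same growth rate, a longer stay gives a higher monthly percentage, because compounding gain is divided by elapsed time. A less mature donor-milk group could therefore show an inflated figure that hides an advantage of own mother's milk. A less mature own-milk group could show an advantage that is not due to the milk. The main objective of the study rests on this contrast.

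**Working it through.** **1. Text.** Sections 2.1 and 2.2 give a non-randomised comparison of self-formed groups. Section 2.7 gives covariate-free tests for group contrasts and possible adjustment for correlations. No regression, ANCOVA, matching, stratification or propensity method appears for the growth outcome. Section 2.7 does not name the primary outcome. That its tests apply there is inferred from two facts: they are the only between-group methods given, and the sample size rests on a two-group comparison.

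**2. The plan's own figure.** The plan says "18 infants per group were needed to achieve a power of 90% with an alpha error of 5" per cent. Taking SD = IQR/1.349 (normality assumed):
- PI-DHM: 30/1.349 = 22.24. PI-OMM: 21/1.349 = 15.57.
- Mean variance = (494.6 + 242.3)/2 = 368.4, so SD = 19.19.
- n = 2 × (1.960 + 1.282)² × 368.4 / 11² = 2 × 10.51 × 368.4 / 121 = 64 per group.

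The stated 18 is not reproduced. That is a separate matter, and nothing below depends on it.

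**3. How the endpoint moves with length of stay (assumed model).** Let E(T) = (exp(rT) − 1)/T, with T in months of 30.44 days. Fix r so that E(T) = 0.52, i.e. r = ln(1 + 0.52T)/T. Then find the longer stay T′ at which the same r gives 0.63.

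| T (months) | r | T′ | extra days | points per week = 11/(days/7) |
|---|---|---|---|---|
| 1.0 | 0.419 | 1.835 | 25.4 | 3.0 |
| 1.5 | 0.384 | 2.389 | 27.1 | 2.8 |
| 2.0 | 0.357 | 2.940 | 28.6 | 2.7 |
| 2.5 | 0.333 | 3.490 | 30.1 | 2.6 |

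If infants go home near a common postmenstrual age (assumed), one week less gestation means one week more stay. At 2.7 points per week, mean imbalances of 1, 2 and 3 weeks give 2.7, 5.4 and 8.1 points.

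**4. Effect on the unadjusted test.** Section 3 reports 17 PI-DHM and 28 PI-OMM infants completing.
- SE = √(22.24²/17 + 15.57²/28) = √(29.09 + 8.65) = 6.14.
- With no milk effect and bias b, the rejection rate is Φ(−1.96 + b/SE) + Φ(−1.96 − b/SE).
- b = 2.7: 7.2%.
- b = 5.4: b/SE = 0.879, so Φ(−1.081) + Φ(−2.839) = 0.140 + 0.002 = 14.2%.
- b = 8.1: 26.1%.
- A Welch t-test gives 7.1%, 13.5% and 24.5%.

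Masking: with a true difference of 11 and a bias of 5.4 the other way, the expected difference is 5.6. The rejection rate is then 14.9%, against 43.3% without bias (normal approximation).

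**5. A check without the growth model.** Spurious difference = ρ × standardised imbalance × 19.19, where ρ is the covariate–outcome correlation. For assumed ρ of 0.3 to 0.7 and imbalance of 0.2 to 0.8 SD, this is 1.2 to 10.7 points, with rejection rates of 5.4% to 42%. At ρ = 0.5 and 0.5 SD it is 4.8 points and 12%.

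**6. Does adjustment gain power?** An imbalance of d within-group SDs inflates the variance of the adjusted estimate by 1 + (17/45)(28/45)d², which is 1.24 at d = 1 and 1.53 at d = 1.5. The unadjusted Welch test has 41% power for 11 points. With covariates explaining 20, 30 or 40% of the variance (assumed), adjusted power is:
- no imbalance: 49, 54 and 60%;
- d = 1: 41, 46 and 52%;
- d = 1.5: 34, 38 and 44%.

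**The case against.** Section 2.7 is a short, generic paragraph in a condensed article. It does not name the primary outcome or rule out adjusted analyses, and covariate lists are usually left to an analysis plan that is not shown. The absence of a covariate list would indeed be no finding. What stands is narrower: the article does choose methods. It assigns group contrasts to covariate-free tests and attaches adjustment to correlations, so an adjusted primary model would change the stated choice.

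A reader might go further and infer that the growth comparison will be biased, or biased in favour of own mother's milk. The documents do not support that. They give no baseline data by group, so neither the existence nor the direction of an imbalance is known. The figures rest on an assumed growth curve, stay lengths, endpoint formula and imbalances. A 3-week mean difference would also be large when both groups are capped below 32 weeks.

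A reader might also infer that adjustment would rescue power. It would do so only if the groups are balanced. Where imbalance is large, and adjustment matters most, the gain shrinks or reverses. Nor would adjustment for a few measured covariates by itself establish a causal milk effect.

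**Conclusion.** The point holds in conditional form. As written, the plan has no means of separating milk from maturity or birth size in its main contrast. If the preterm groups differ on either, the unadjusted result cannot be read as an effect of milk type. The 2-week illustration amounts to about half the planned difference (5.4/11 = 49%) and nearly triples the nominal 5% error rate. It is conditional on the assumptions listed in the working and is not an estimate for this cohort. The conclusion itself needs only the stated design and the stated tests.

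**What to change.** Make the primary PI-OMM versus PI-DHM analysis a pre-specified linear regression of the growth outcome on group. Adjust for gestational age, birth-weight z-score and sex, and for multiple birth if it was recorded. Report the adjusted difference with a 95% confidence interval and small-sample robust standard errors such as HC3, since the spreads differ and the smaller group has 17 infants. Keep the unadjusted test as descriptive. State that residual confounding, for example by illness or delivery circumstances, remains.

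Cost: wording and a little more analysis, with no new infants. Gestational age and sex are in Table 1, and birth weight is needed for the endpoint itself. Multiple birth is not listed anywhere in the article, so its availability must be checked. The interval may be wider if the groups are imbalanced, and no gain in power is claimed.
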